## Study objectives

The objective of this study is to evaluate whether imaging surveillance frequency might have been safely reduced in a selected group of EVAR patients, for example, in patients with an asymptomatic or symptomatic infrarenal AAA who underwent EVAR and who had no abnormalities on the 3-month postoperative CTA. The clinical course of a large cohort of patients will be evaluated with follow-up ranging between 6 and 11 years. Baseline patient characteristics, aortic anatomy and details of the operation will be derived from the patient’s medical record. The first milestone during follow-up is the first postoperative CTA. This scan either shows complications such as endoleaks, malposition or migration of the graft, or the absence thereof. All follow-up visits, imaging studies, as well as all interventions after EVAR and outcomes will be registered. Our hypothesis is that patients with less follow-up will have better outcomes regarding the number of interventions and aneurysm-related mortality compared to patients with annual follow-up. Regarding the intervention rates, it is expected that adherence to imaging surveillance may detect more abnormalities triggering re-interventions which in itself may cause additional complications and perhaps even a decrease in survival rates. We hypothesise that the need for routine imaging for patients with no abnormalities at their initial CTA can be decreased.

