**Figure 1 F1:**
[figure not shown]
Patient subgroups. AAA, abdominal aortic aneurysm; CTA, CT angiography; EVAR, endovascular aneurysm repair.

The standard of care is defined by the current guidelines and IFU. The usual follow-up schedule in the IFU is: CTA and abdominal X-ray at 30 days, 6 and 12 months and yearly thereafter. The 2019 ESVS guidelines recommend a CTA 30 days after EVAR. If there is adequate seal and no endoleak, patients are classified as low risk and CTA follow-up may take place 5 years later. If there is an inadequate seal and endoleak type I/III patients could be either evaluated for re-intervention or if sac shrinkage occurs yearly DUS is recommended. In the 2018 SVS guideline, CTA at 1 and 12 months is recommended and if neither endoleak nor sac enlargement is documented, DUS is suggested for annual postoperative surveillance. In our study design, the definition of compliance is undergoing imaging surveillance every 16 months since patients in most centres will be rescheduled if they missed their annual follow-up visit. Device-specific complications after EVAR will also be examined.

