### Study procedures

The primary outcomes of this study are interventions and aneurysm-related mortality for patients who had a normal initial postoperative CTA and who do adhere to our definition of yearly imaging surveillance over a 6-year to 11-year follow-up period, compared to those who do not adhere to our definition.

Interventions are EVAR-related interventions defined by the SVS reporting standards as postoperative adjunctive manoeuvres.^16 17^ Interventions for wound complications at the access site are not included, since these are detectable without the use of imaging.

Date of death during follow-up, if applicable, will be obtained from patient medical records and verified by the Dutch municipal personal records database (GBA).

Details of all surveillance imaging are obtained from patient medical records and radiology reports. The time between imaging appointments is calculated to determine whether patients adhere to this studies definition of with yearly imaging surveillance, that is, within every 16 months.

Date, type, indication and outcome of all postoperative imaging during follow-up are obtained from patient medical records, specifically imaging order forms and radiology reports. A normal initial postoperative CT scan is defined as a CT scan which shows no endoleaks, endograft migration (>10 mm), kinking or obstruction. All imaging outcomes are based on the report compiled by radiologists. These reports will not be re-evaluated by an independent radiologist, since we want to base our outcomes on real life data.

Secondary outcomes are all-cause mortality, type I, type II, type III and type IV endoleak, graft or outflow (iliac) occlusion, aneurysm rupture and endograft infection. This is also obtained from patient medical records, specifically radiology reports and Dutch municipal personal records database (GBA).

Date of aneurysm rupture is obtained from patient medical records, specifically operative reports, radiology reports and progress notes.

Costs of all EVAR-related imaging and outpatient clinic visits will be calculated per patient. Cost is defined as volume times price. Prices from the ‘Cost manual of the Dutch Health Care Institute’’ will be used. Costs for the patients will also be included. The quality-adjusted life years, a generic measure of disease burden including both the quality and quantity of life, cannot be calculated with this retrospective design.

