### Statistical methods

Differences in baseline characteristics between patients undergoing or not undergoing yearly standardised imaging surveillance by either CTA or DUS, will be analysed using the χ^2^ or Fisher's exact test for categorical variables and the student's t-test or Mann-Whitney test for continuous variables, if appropriate.

The primary endpoints, that is, survival and freedom from intervention will be estimated by Kaplan-Meier survival analysis and differences between groups will be assessed with the log-rank test.

Secondary endpoints such as freedom from aneurysm rupture between patients with and without yearly standardised imaging surveillance will be estimated by Kaplan-Meier survival analysis, and differences between these groups will be calculated with the log-rank test.

Multivariable cox regression analysis will be used to determine survival and the freedom of intervention corrected for age, gender, AAA diameter, ASA classification, neck length, neck angulation and type of endograft. The association between postoperative intervention and the following covariates will be investigated with the multivariate Cox-regression analysis:

Age.Gender.AAA diameter.ASA classification.Neck length (>15 mm).Neck angulation (>60°).Type of endograft.Initial postoperative CTA.

All statistical analyses will be done with SPSS software (IBM, V.25). The level for statistical significance is set at a p value <0.05. The proportion of missing data will be displayed. The missing values will be imputed by multiple imputation techniques if this does not exceed 10%–15% and conduct a sensitivity analysis to investigate the effect of the missing data on the results of the analysis. If missing data on outcome variables exceeds 15%, we plan to perform subgroup analysis.

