Our study is subject to limitations due to the nature of administrative data and its retrospective and observational design. As with all studies using administrative data, it allows only the collection of data that was documented in patient medical records. It is also possible that some patients may have transferred to alternative surveillance protocols in different medical centres without our knowledge. The study will assess results in 17 medical centres over 11 years, during which time improvements in endograft and in clinical practice has occurred. Attrition bias due to loss to follow-up represents a threat to the internal validity of our cohort study. The mentioned e-survey has only been sent to participating vascular surgeons, perhaps surgeons participating in the ODYSSEUS study strongly believe that imaging surveillance frequency can be reduced. This may have provided a biased view of post-EVAR follow-up in the Netherlands. However, most of the high-volume EVAR centres in the Netherlands have been included. Another limitation is that no information is retrieved from patients’ medical records about when not to intervene and what the reason was for this decision.

In conclusion, with the ODYSSEUS study we aim to confirm the follow-up protocol of the recent ESVS guideline delaying imaging after 5 years if classified in the low risk group and therefore aim to investigate the intervention-free-survival and aneurysm-related mortality for patients with and without yearly imaging surveillance.

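### Freedom from aneurysm rupture is compared between non-randomised imaging groups by log-rank alone, while survival and intervention also get covariate adjustment; baseline imbalance could hide or exaggerate a rupture difference

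*Protocol article*

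**What the plan says.** The Statistical methods section assigns methods by outcome.

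- **Rupture.** "Secondary endpoints such as freedom from aneurysm rupture between patients with and without yearly standardised imaging surveillance will be estimated by Kaplan-Meier survival analysis"; then "differences between these groups will be calculated with the log-rank test". No covariates, strata, matching or weights are named.
- **Survival and intervention.** After their own Kaplan-Meier and log-rank step, a further model is given: "Multivariable cox regression analysis will be used to determine survival and the freedom of intervention corrected for age, gender, AAA diameter, ASA classification", and also neck length, neck angulation and type of endograft.
- **A second Cox model.** "The association between postoperative intervention and the following covariates will be investigated with the multivariate Cox-regression analysis". Its outcome is again intervention, not rupture.

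The groups arise from observed imaging. Below Figure 1 (General study design) the article says that "the definition of compliance is undergoing imaging surveillance every 16 months since patients in most centres will be rescheduled if they missed their annual follow-up". General study design separates patients with a normal first CTA into those with yearly imaging (A) and those without (B); patients with an abnormal first CTA form group C.

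Study procedures lists rupture among the secondary outcomes: "graft or outflow (iliac) occlusion, aneurysm rupture and endograft infection". The stated objective is to "evaluate whether imaging surveillance frequency might have been safely reduced in a selected group of EVAR patients" (Study objectives).

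**The concern.** By correcting survival and intervention for age, gender, AAA diameter, ASA class, neck anatomy and device, the plan accepts that the imaging groups may differ on these factors and that they may affect outcome. Rupture is also an event of the aneurysm and the device, yet the article gives no reason for leaving it uncorrected.

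The study asks whether less imaging is safe, and rupture bears on that directly. Intervention does so less, because Study objectives itself expects imaging to trigger more of it. A crude log-rank p-value for rupture can mislead in two ways. Imbalance can move the estimate in either direction. With few events, a non-significant result may be taken as reassurance when the data could not have excluded a material excess.

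**Working it through.** **1. The plan's own figures.** The intervention sample size uses 75% v 82% at 7 years, 90% power and alpha 0.05. With unpooled variance and a two-sided test:

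n = (1.960 + 1.282)² × (0.75 × 0.25 + 0.82 × 0.18) / 0.07² = 718.6, so 719 per group and 1438 in total, as stated. No event count or power is stated for rupture, so these figures neither support nor refute the point. The 1438 serves below only as the planned size of A plus B.

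**2. Which outcomes are adjusted.**

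| Outcome | Kaplan-Meier and log-rank | Covariate-corrected Cox |
|---|---|---|
| Survival | yes | yes |
| Freedom from intervention | yes | yes |
| Freedom from rupture | yes | not named |

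**3. How far imbalance could move the crude ratio (assumed inputs).** The documents give neither a rupture rate nor any imbalance. Take one binary high-risk feature with rupture hazard ratio h and prevalence pA in group A and pB in group B. For a rare event:

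crude ratio (B v A) = true ratio × [1 + pB(h − 1)] / [1 + pA(h − 1)]

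With no true effect (true ratio 1):

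| Prevalence A v B | h | Crude B v A |
|---|---|---|
| 30% v 20% | 2 | 1.2/1.3 = 0.92 |
| 40% v 20% | 4 | 1.6/2.2 = 0.73 |
| 20% v 30% | 2 | 1.3/1.2 = 1.08 |
| 20% v 40% | 4 | 2.2/1.6 = 1.38 |

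If group B truly had 30% more ruptures (true ratio 1.3), the crude ratio would be 1.3 × 0.923 = 1.20 down to 1.3 × 0.727 = 0.95 in the first two rows. In the last two it would be 1.3 × 1.083 = 1.41 up to 1.3 × 1.375 = 1.79. The same mechanism therefore conceals the excess in one direction and inflates it in the other.

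**4. How many ruptures there might be (assumed 1 to 3%).**

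| Rupture | Events in 1438 | Events per parameter (8) | Power for hazard ratio 2 |
|---|---|---|---|
| 1% | 14 | 1.8 | 26% |
| 2% | 29 | 3.6 | 46% |
| 3% | 43 | 5.4 | 62% |

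The eight parameters are group plus the seven listed covariates, one each; a multi-level device or ASA variable would add more. Power is by Schoenfeld's formula (two-sided 0.05, 1:1). For 80% power the events needed are 4 × (1.960 + 0.842)² / (ln 2)² = 65.3, so 66.

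Two things follow. An ordinary Cox model with all seven covariates would be overfitted, so adjustment needs another form. And even a doubling of rupture would often give a non-significant log-rank.

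**The case against.** **The article is condensed.** Its rupture sentence is illustrative and never says that secondary outcomes will go unadjusted; an analysis plan not shown here may add a model. That limits the claim to what this document states. It does not remove it: a method is fixed for a named endpoint, and the sentence after it gives adjustment to other outcomes.

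**Rupture is secondary.** A reader might infer that rupture is the plan's main safety test. It is not. Aneurysm-related mortality is a primary endpoint and carries the 3% non-inferiority margin (Sample size and power), whereas rupture has no margin, power or decision rule. This lowers the weight of the point. It also raises a neighbouring question: whether the word survival in the Cox sentence covers aneurysm-related mortality.

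**The direction is unknown.** A reader might infer that higher-risk patients were imaged more, so that the crude test would make less imaging look safe. Nothing in the article says so. Background and relevant literature and data reports missed appointments, force majeure and centre-specific protocols, with one centre already on five-yearly imaging. For the same reason the groups are best called non-randomised rather than self-selected.

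**A v B is limited to a normal first CTA.** This removes endoleak, migration, kinking and obstruction at that scan from the contrast. It does not balance age, ASA class, diameter, neck anatomy or device.

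**Imbalance and design limits are acknowledged.** Baseline differences will be tested, and the Discussion concedes: "Our study is subject to limitations due to the nature of administrative data and its retrospective and observational design". Neither step alters the rupture comparison.

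**Few ruptures make adjustment fragile.** This stands. It is a reason to choose a suitable method and to report imprecision, and it applies equally to reading the crude test.

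**Conclusion.** The point holds as a moderate weakness in a secondary safety analysis. The article fixes an uncorrected rupture comparison between non-randomised groups while correcting survival and intervention for seven baseline factors. Imbalance in those factors could hide or exaggerate a rupture difference. Under the assumed prevalences (20% v 30 to 40%) and hazard ratios (2 to 4), the crude ratio with no true effect is 0.73 to 0.92 or, reversed, 1.08 to 1.38. These ranges are illustrations, not estimates for this cohort.

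The documents do not support the stronger conclusion that the crude test is biased towards showing less imaging as safe. Nor would baseline adjustment make the comparison sound by itself: groups defined by imaging during follow-up, and deaths from other causes, are separate sources of bias that it leaves in place.

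**What to change.** In Statistical methods:

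1. Add a pre-specified adjusted comparison of freedom from rupture between groups A and B, in a form that suits few events. Options are propensity-score weighting or stratification on the baseline covariates already listed (age, gender, AAA diameter, ASA class, neck length, neck angulation, endograft type), or a penalised Cox model.
2. Report the hazard ratio and the 7-year risk difference with 95% confidence intervals beside the crude log-rank.
3. State that a non-significant log-rank for rupture will not be read as evidence of safety.
4. State with the result that adjustment does not remove bias from defining groups by imaging during follow-up, or from competing death.

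**Cost.** A few lines of text and one extra model on covariates the plan already uses. Confidence intervals will be wider, possibly much wider, because a few heavily weighted ruptures can dominate. A propensity score models group membership, so it is less constrained by the number of ruptures. However, 719 v 719 is a planning assumption, and actual group sizes depend on observed adherence. No stated sample size changes.

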### Background and relevant literature and data

Before initiating the ODYSSEUS study, we conducted a survey among Dutch vascular surgeons to find out if they support the possibility of reducing the frequency of imaging surveillance. In this survey, vascular surgeons reported the main reasons patients did not comply with follow-up visits, that is, they had forgotten the appointment or were prevented by force majeure. Most physicians estimated that less than 10% of their patients had missed one or more follow-up visits post-EVAR. This might be an overestimation of the true adherence to follow-up visits, as these observations are in contrast with a study reporting that only 43% of patients had complete surveillance.^4^

We also asked participating vascular surgeons to upload their standard post-EVAR protocol to investigate if there were differences between centres in the Netherlands. In all centres, imaging took place within the first 3 months after surgery, mostly by CTA. Most centres comply with their own post-EVAR surveillance protocols which have many commonalities with the SVS and ESVS guidelines. Only one centre uses precisely the same post-EVAR surveillance protocol as recommended by the SVS guidelines. Another centre had already reduced follow-up imaging to once every 5 years, using either CTA or DUS as is stated in the new ESVS guidelines.^3^ While vascular surgeons still seem to adhere to their hospital-specific protocol, they do support the need for reducing follow-up by selecting a group of patients for which yearly follow-up can safely be omitted. However, some surgeons indicated that more evidence is needed than is available in the current literature.^6 7^

In studies that have investigated the indications for post-EVAR intervention, it is stated that 61%–98% of interventions were necessary because of symptoms and not because of findings at surveillance imaging. This suggests that post-EVAR surveillance protocols provide no benefit to a large group of patients, as complications occur in between surveillance visits.^8 9^ Imaging surveillance may even lead to unnecessary interventions and it does not appear to be associated with improved survival.^9 10^ We hypothesise that the requirement for routine imaging for patients at low risk can be reduced. However, novel endovascular devices still require more intensive surveillance as the short- and long-term results of those devices remain undetermined.

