### General study design

A multicentre retrospective cohort study in 17 medical centres in the Netherlands. Data will be collected from the medical records of all consecutive patients with AAA who underwent EVAR between January 2007 and January 2012. This selection provides a theoretical length of follow-up of 6–11 years on December 2018. Patients will be divided into three groups: (A) patients without abnormalities at their first postoperative CTA with yearly imaging surveillance, (B) patients without abnormalities at their first postoperative CTA without yearly imaging surveillance and (C) patients with abnormalities at their first postoperative CTA (figure 1). This retrospective design has the advantage of collecting long term follow-up data. The Dutch Dream trial found that the number of interventions starts to rise 4 years after EVAR and the long-term results of the EVAR-1 trial show that EVAR has an early survival benefit but inferior late survival compared to open surgical repair.^13 14^ This is in contrast to the recently published long-term results of the OVER trial in which no difference was observed between EVAR and OSR in the primary outcome of all-cause mortality.^15^ Hence, a prospective study would take approximately 8 to 10 years to gather enough patients with adequate follow-up.

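### The listed Cox covariates omit centre and year of EVAR, so differences between hospitals may confound the comparison of groups A and B

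*Protocol article*

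**What the plan says.** **Design.** The General study design section describes "A multicentre retrospective cohort study in 17 medical centres in the Netherlands". EVAR dates run from January 2007 to January 2012, with follow-up to December 2018. Groups A and B both have a normal first postoperative CTA. They differ in whether the patient's imaging meets the 16-month rule.

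**Analysis.** Under Statistical methods, groups are compared by log-rank test. Survival and freedom from intervention are then modelled by Cox regression "corrected for age, gender, AAA diameter, ASA classification, neck length, neck angulation and type of endograft". A second list, for the association with postoperative intervention, adds only the initial postoperative CTA. The article nowhere mentions centre as a covariate, stratum or frailty, clustered variance, or year of EVAR.

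**Centre and exposure.** The Background section says that "vascular surgeons still seem to adhere to their hospital-specific protocol". It reports that only one centre follows the SVS schedule exactly, and that "Another centre had already reduced follow-up imaging to once every 5 years". It also says: "Most centres comply with their own post-EVAR surveillance protocols which have many commonalities with the SVS and ESVS guidelines".

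**Change over time.** The Discussion names as a limitation the 11-year period, "during which time improvements in endograft and in clinical practice has occurred". It gives no analytic remedy.

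**The concern.** Confounding by centre needs two links.

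- **Centre to exposure.** The article documents this one: surveillance follows a hospital's own protocol. The section General study design also justifies the 16-month rule by how most centres rebook missed visits.
- **Centre to outcome.** This one is plausible but not shown. The sites mix university and general hospitals. The first CTA is judged from local radiology reports that are not re-read. The Discussion states that decisions not to intervene, and the reasons for them, are not retrieved, so the local threshold for re-intervention is unmeasured. Type of endograft captures device choice but not that threshold.

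If both links hold, part of the difference between A and B is a difference between hospitals, and it would be read as an effect of surveillance in a study meant to inform whether less imaging is safe. Year of EVAR raises the same issue more weakly. Separately, if imaging and outcome both cluster by centre, standard errors that treat patients as independent are too optimistic.

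**Working it through.** **1. The plan's own figure.** Inputs from Sample size and power: 75% versus 82% intervention-free at 7 years, 90% power, alpha 0.05. With unpooled variance, two-sided:

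n = (1.960 + 1.282)² × (0.75×0.25 + 0.82×0.18) / 0.07² = 718.6, so 719 per group and 1438 in total.

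This agrees with the article and is not disputed. It makes no allowance for centre. Under proportional hazards the planned effect, yearly versus not yearly, is ln(0.75)/ln(0.82) = 1.45.

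**2. Possible understatement of the standard error.** Average centre size among A and B is m = 1438/17 = 84.6. Exposure is defined per patient, so the approximate variance inflation is 1 + (m − 1) × ICC(outcome) × ICC(exposure). The article gives neither ICC. Over assumed ranges:

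| Exposure ICC | Inflation at outcome ICC 0.01 | Inflation at outcome ICC 0.05 |
|---|---|---|
| 0 | 1.00 | 1.00 |
| 0.05 | 1.04 | 1.21 |
| 0.10 | 1.08 | 1.42 |
| 0.30 | 1.25 | 2.25 |

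At the top of this range the true standard error is √2.25 = 1.50 times the stated one. An analysis that ignores centre would then have a two-sided error of about 0.19. One that allows for it would have about 58% power at 719 per group. At the bottom nothing changes.

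**3. Bias, by simulation.** Assumptions: 17 centres of equal expected size, 1438 patients, true hazard ratio 1, a 7-year intervention-free rate of 78% at an average centre, censoring between 6 and 11 years, no other covariates, 1000 runs per setting. SD(x) is the between-centre SD of the log-odds of yearly imaging. SD(y) is that of the log hazard. The correlation is between the two centre effects.

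| SD(x) | SD(y) | Correlation | HR without centre | Empirical SD / model SE | Rejection | HR stratified | Rejection |
|---|---|---|---|---|---|---|---|
| 0 | 0.3 | 0 | 1.00 | 0.106 / 0.103 | 5.6% | 1.00 | 6.3% |
| 0.5 | 0.3 | 0 | 1.00 | 0.109 / 0.103 | 7.0% | 1.00 | 5.8% |
| 1 | 0.3 | 0 | 1.00 | 0.117 / 0.103 | 7.8% | 1.00 | 3.7% |
| 1 | 0.5 | 0 | 1.00 | 0.140 / 0.101 | 17.1% | 1.00 | 4.8% |
| 1 | 0.3 | +0.5 | 1.13 | 0.117 / 0.103 | 23.6% | 1.00 | 4.2% |
| 1 | 0.3 | −0.5 | 0.88 | 0.119 / 0.103 | 25.2% | 1.00 | 5.4% |

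SD(x) = 1 corresponds to an exposure ICC of about 0.23 on the latent scale. Without correlation there is no bias, and the standard-error shortfall runs from 1 − 0.103/0.106 = 3% to 1 − 0.101/0.140 = 28%. With a correlation of ±0.5 the bias on the log scale is ln(1.13)/ln(1.45) = 0.33 or ln(0.88)/ln(1.45) = −0.34, about a third of the planned effect in either direction.

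**The case against.** **Similar protocols, patient-level exposure.** The survey describes much in common between centres with one clear outlier. The main reasons it gives for missed visits (forgetting, or circumstances beyond the patient's control) act on individual patients. It also records practice when the survey was done and does not say when the outlying centre changed its schedule. All of this stands, and it limits the size of the problem. It does not remove the documented link between hospital and imaging.

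**Standard errors.** A reader might infer that the standard errors are definitely too small, or apply the full design effect 1 + (m − 1) × ICC, which is 1.84 at ICC 0.01 and 5.18 at ICC 0.05. The documents do not support either reading. The full design effect needs adherence to be set wholly by centre, and in that case a centre-stratified model could estimate nothing.

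**The 3-point margin.** A reader might also infer that an interval compared with the mortality margin would be too narrow. The margin appears only in the sample size text, and Statistical methods specifies no such interval.

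**Year of EVAR.** The operations span only 5 years, and type of endograft already carries part of the device change. This stands: the argument for year is weaker than the argument for centre.

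**Left to a fuller document.** Clustered variance and sensitivity analyses are details an article may omit, and their absence alone would be no finding. The covariate list is different, because it is stated by name without centre or year.

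**Stratification has its own limits.** It discards variation in policy between centres and leaves non-adherence within centres, which may be confounded by frailty. This is a fair reason to report both models.

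**Conclusion.** The point holds as a risk that the stated model leaves uncontrolled; no bias has been demonstrated. Centre is a documented influence on imaging frequency and a plausible, unmeasured influence on intervention, and it is missing from a named adjustment set. The direction and size of the bias are unknown. The hazard ratios of 1.13 and 0.88 rest on the assumed correlation of ±0.5 and the assumed spread between centres, and with no correlation there is no bias. Standard errors may be understated by anything from a negligible to a material amount. The case for adding year of EVAR is modest. The change is worth making because it is cheap and would show whether centre matters.

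**What to change.** - Stratify the adjusted Cox models by centre, or use a shared centre frailty.
- Add year of EVAR to the covariates.
- Report a centre-stratified log-rank test beside the planned one, and the unstratified Cox model beside the stratified one, so that readers can see how far the estimate moves.

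Centre-clustered standard errors alone would not be enough: they leave the confounding in place, and with only 17 clusters they can themselves be too small.

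**Cost.** Centre and operation date should already be held for every patient, so no new data are needed. Intervals widen slightly: in the simulation the stratified model's standard error was 0.104 against 0.103 with no clustering of exposure, and 0.114 against 0.103 (about 11% more) at SD(x) = 1 and SD(y) = 0.3. Centres with nearly all their patients in one group contribute little to the stratified estimate.

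### The A v B comparison adjusts only for factors known by the time of EVAR, so findings during follow-up that lead to both imaging and intervention can bias it towards fewer interventions in B

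*Protocol article*

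**What the plan says.** General study design splits patients with a normal first CTA by later imaging; the second of the two groups is "B) patients without abnormalities at their first postoperative CTA without yearly imaging surveillance". Below Figure 1, "the definition of compliance is undergoing imaging surveillance every 16 months". Study procedures states how membership is found: "The time between imaging appointments is calculated to determine whether patients adhere". The primary comparison there sets patients "who do adhere to our definition of yearly imaging surveillance over a 6-year to 11-year follow-up period" against those who do not. Exposure is therefore decided after baseline.

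Statistical methods then fixes the analysis. Survival and freedom from intervention "will be estimated by Kaplan-Meier survival analysis and differences between groups will be assessed with the log-rank test". A multivariable Cox model for the same two outcomes is "corrected for age, gender, AAA diameter, ASA classification, neck length, neck angulation and type of endograft". A second Cox list, for the association with intervention, adds the initial postoperative CTA. No time-varying term or weighting is stated.

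Study procedures also says that the date, type, indication and outcome of every postoperative scan are extracted.

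**The concern.** Nobody is allocated to imaging. What a scan shows can change both when the next scan takes place and whether the patient is treated. The protocol describes both links. Study objectives expects surveillance to find abnormalities that trigger re-intervention. The guideline summary below Figure 1 has endoleak, seal and sac behaviour determining later imaging.

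A patient with a new abnormality is thus more likely to stay on schedule, in A, and more likely to have an intervention. Adjusting for age, anatomy and graft type does not remove this. The initial CTA is normal in A and B by definition, so it adjusts nothing in this comparison.

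The resulting bias on interventions points the same way as the study's hypothesis that less follow-up means fewer interventions. At stake is whether a lower intervention rate in B can be read as a consequence of less imaging.

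**Working it through.** **1. The planned effect.** Sample size and power gives 75% and 82% intervention-free at 7 years, 90% power and a 0.05 level. With the unpooled formula and a two-sided test:

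n = (1.960 + 1.282)² × (0.75×0.25 + 0.82×0.18) / 0.07² = 718.6, so 719 per group, as stated.

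Under proportional hazards the implied hazard ratio (HR), B v A, is ln 0.82 / ln 0.75 = 0.69. This is the yardstick for the bias.

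**2. When each variable is known.**
- Exposure: after the first CTA, from imaging gaps over follow-up.
- Outcome: over the same period.
- Covariates named in Statistical methods: at or before EVAR, apart from the first CTA, which is constant across A and B.
- Later endoleak or sac change: after baseline, linked in the protocol to both imaging and intervention, and absent from the model.

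**3. Illustration with no effect of imaging.** The inputs are assumptions; the documents give none.
- A new abnormality arises in 2% or 4% of patients per year.
- The yearly risk of a late scan is 12% without an abnormality, and 2% or 6% with one.
- The yearly risk of intervention is 2% without, and 10% or 25% with.
- There are seven yearly intervals. Exposure is updated each year as having lapsed at any time so far. The model is a discrete-time complementary log-log hazard model with 200,000 patients per scenario.

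The time-updated exposure keeps this bias apart from a separate one that arises when patients are classified over the whole of follow-up.

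| Abnormality per year | Late scan, with abnormality | Intervention, with abnormality | HR B v A (true value 1) |
|---|---|---|---|
| 2% | 2% | 10% | 0.87 |
| 2% | 2% | 25% | 0.76 |
| 2% | 6% | 10% | 0.91 |
| 2% | 6% | 25% | 0.83 |
| 4% | 2% | 10% | 0.75 |
| 4% | 2% | 25% | 0.68 |
| 4% | 6% | 10% | 0.86 |
| 4% | 6% | 25% | 0.81 |

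The second decimal carries simulation error. Repeat runs put the lowest cell at 0.67 to 0.69 and the highest at 0.90 to 0.92, so the range is about 0.69 to 0.91. Coding exposure as a current lapse instead gives lower values, 0.51 to 0.87.

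**4. A second set of assumptions.** Abnormality 4% per year; intervention hazard 2% without, and 5% or 15% with; yearly imaging probability 0.6 without an abnormality. HR, not imaged v imaged:
- imaging probability 0.6 with an abnormality (no link): 1.00 and 0.99
- 0.7: 0.96 and 0.84
- 0.8: 0.89 and 0.72
- 0.9: 0.81 and 0.59

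The bias disappears when findings do not drive imaging. One of the six linked settings falls below 0.69.

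**5. Does the remedy work?** In the step 3 scenarios, stabilised inverse-probability weights for staying on schedule brought the HR back to 0.97 to 1.02 (100,000 patients per scenario).

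**The case against.** The strongest reply is that imaging that finds abnormalities and so leads to intervention is the very effect the study expects, so an HR below 1 is not all bias. That stands in part, and it is why findings should not simply be entered as Cox covariates. But the simulations set that effect to zero and the HR still falls below 1. The planned analysis cannot tell the two sources apart.

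A second reply is that weighting is a detail for an analysis plan, and that the Discussion already concedes limits from the observational design. The article, however, names its tests, covariates and software, and its limitations mention attrition and transfers but not this mechanism.

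Four stronger readings are tempting and are not supported:
- **The bias is as large as the planned effect.** In the table only one corner reaches 0.69, and there 58% of interventions follow the abnormality. The Background cites 61–98% of interventions as symptom-driven, leaving 2–39% for surveillance findings. Scenarios with a share of at most about 40% give 0.76 to 0.91. This limit is not firm: a symptomatic patient may also have a known abnormality, and the current-lapse coding falls to 0.66 within it.
- **Any scan counts towards the 16 months.** The protocol speaks of surveillance imaging and imaging appointments. It only fails to exclude scans prompted by symptoms or a known finding.
- **The log-rank test outranks the Cox model.** Statistical methods plans both and ranks neither. Age and ASA class in the Cox model also partly cover frail patients who stop attending.
- **Centre must be a stratum.** Protocols differ ("Another centre had already reduced follow-up imaging to once every 5 years"), but that variation is not driven by a patient's own findings. Stratifying discards it and leaves mainly within-centre lapses, which are more open to this confounding.

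**Conclusion.** The concern holds for the intervention endpoint. As written, the A v B comparison leaves confounding by findings during follow-up uncontrolled, and the bias favours the study's own hypothesis. This rests on one assumption that the protocol itself makes plausible: findings raise both the chance of on-time imaging and the chance of intervention.

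The size is unknown. Under the assumed inputs, with exposure updated as ever lapsed, the HR with no imaging effect is about 0.69 to 0.91 against a planned 0.69. Equality with the planned effect is a worst case under that coding, not an estimate. The protocol does not state a time-updated exposure, so these figures illustrate the mechanism and do not predict the study's result.

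A reader might extend the direction to aneurysm-related mortality. The documents do not support that: patients with abnormalities who stay in A would favour B, while frail patients who lapse into B may do the opposite. The sample size arithmetic is unaffected.

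**What to change.** 1. Base the A v B conclusion on the adjusted comparison and present the log-rank test as descriptive.
2. State that only scheduled surveillance scans, identified by the recorded indication, count towards the 16 months.
3. Add an analysis with exposure updated over time and stabilised inverse-probability weights for staying on schedule. Build the weights from the last recorded scan outcome: endoleak, and sac change where reported. Do not enter these as ordinary Cox covariates, because their detection depends on imaging.
4. Name this confounding in the limitations.

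Centre can be examined in a sensitivity analysis.

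The cost is more analysis work, wider intervals and possibly software beyond SPSS. Scan indication and outcome are already to be extracted. Sac change is not a named endpoint and may be recorded unevenly, and intercurrent illness is not listed as collected. A patient who has lapsed has no newer scan to update from. The weights remove only confounding by recorded findings, so they reduce the bias without guaranteeing its removal.
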